### Data management, monitoring and auditing

All data will be collected in electronic case report forms (eCRF). The eCRF will be implemented in a Good Clinical Practice (GCP)-compliant clinical data management system with electronic data capture functionality, which provides the capability to perform the major data management activities within a consistent, auditable and integrated electronic environment (query management, data entry, data validation). Range, validity and consistency checks will be implanted in the eCRF for application during data entry. All data entry, modification or deletion will be recorded automatically in an audit trail indicating the original value, the new value, the reason for change, who made the change and when the change was made. A digital signature is implemented and included in the audit trail. Periodically, central monitoring of the data is performed and actions are taken to ensure data quality (queries, re-training). Implementation of the eCRF has been performed by data managers in cooperation with biostatisticians from the Coordination Center for Clinical Trials. All procedures are documented in the protocol and in the Data Management Manual.

Source data remain in the respective hospital information system. Source documents, in particular documents with plain-text names of the participating patients, are kept under strict control of the investigator at the trial site. They will not be transferred to the sponsor or other persons that are not authorized by the patient in the data protection declaration part of the informed consent form. Data recorded in the eCRF are pseudonymized; the Patient Identification List is kept under strict control at the individual trial sites.

Periodic monitoring of the trial will be performed on site in the trial centers by clinical research associates to ensure the safety of the trial participants, the trial itself as well as the correctness of the collected data. They will check the availability of the patient’s informed consent, adherence to eligibility criteria, adherence to treatment according to the trial protocol, safety parameters and completeness of the trial documents in the trial center. The monitor confirms completed source data verification by electronic signature in the eCRF. Monitoring is described in detail in the Monitoring Manual. The on-site trial monitoring is combined with central monitoring with regular data checks.

To ensure sponsor oversight, audits will be performed by an independent auditor at the sponsor’s request. Especially, the vaccine production and its documentation as well as the correct delivery of the tumor and blood samples will be audited. In case of non-compliance of the study centers an audit can also be performed.

### Advanced therapy medicinal product: DC vaccine

The DC vaccines for the GlioVax trial are produced specifically for each patient according to established standard operating procedures with production permission by the local authorities. The vaccines consist of two autologous cellular components: (1) tumor lysates as a whole-cell source of tumor antigens and (2) monocyte-derived, mature DC.

Lysates are produced from autologous tumor material of the patients obtained from fluorescein-guided surgery (FGS). FGS is an established standard surgical procedure for GBM [57]. Because the “solid” part of the tumor can be identified intraoperatively, high-purity tumor material can be obtained, and only samples with a tumor cell content of at least 60% are used for vaccine production. After resection, tumor material is stored frozen at − 80 °C until processing, which involves mechanical dissection and repeated freeze/thaw cycles to generate the lysate.

DC are generated from monocytes enriched immunomagnetically from non-mobilized leukapheresis products. A two-step serum-free culture system is used, to successively generate immature and mature DC [66, 67]. Monocytes are cultured for 6 days in Teflon bags in the presence of granulocyte-macrophage-colony-stimulating factor and interleukin-4 to generate immature DC, which are loaded with tumor antigens by adding the autologous tumor lysate to the cultures. Maturation of DC is induced during an additional 3-day culture period, using the classical pro-inflammatory maturation cocktail described by Jonuleit et al. [68], containing tumor necrosis factor α, interleukin-1β, interleukin-6 and prostaglandin E2, which allows generation of CD83+, fully mature DC with high purity and potent T-cell stimulatory and T_H_1-polarizing activity. After ex-vivo generation of the tumor-lysate-loaded, mature DC, they are stored frozen until the day of application, on which they are thawed, washed, resuspended in 0.9% sodium chloride solution and transferred into a 1-ml syringe for immediate application.

### Sample size considerations and statistical analysis

The sample size calculation is based on the primary outcome OS. A median OS of 14.6 m has been reported for the control intervention [2, 3]. In eight recent smaller phase I/II trials on newly diagnosed GBM treated with lysate-loaded DC as add-on to radiochemotherapy, median OS of 35.9 months [32], 34.4 months [17], 31.9 months (control group 15.0 months) [35], 30.5 months [45], 28.0 months [30], 27.4 months [38], 24.0 months [28], 18.4 months [34] and 17.0 months (control group 10.5 months) [37] have been reported. Based on a critical appraisal of these data, taken into consideration potential treatment dilution effects for the results from the smaller phase I/II trials, we have assumed a prolongation of OS of 12 months for the vaccination group (OS 26.6 months). When the sample size in each group is 61, with a total number of events required of 87, a 0.050-level two-sided log-rank test for equality of survival curves will have 80% power to detect the difference between a median OS in the control group of 14.6 months vs. 26.6 months in the test group (hazard ratio for death, 0.55).

In order to compensate for dropouts (i.e. patients dropping out prior to 24 months without having an event) the total sample size is planned at 136 patients (i.e. an approximately 10% dropout rate). Mainly due to a tumor content of samples for vaccine production below 60% or unsterile tumor material (7/37 (19%); determined at the Institute for Transplantation Diagnostics and Cell Therapeutics, Düsseldorf) or residual tumor volume above 5 ml upon radiological evaluation (17%; [57]), it is anticipated that approximately 35% of GBM patients will fail to meet inclusion/exclusion criteria after resection. Therefore, 210 patients have to be screened to allow for enrollment of 136 patients in the trial.

Each year, about 450–500 patients with newly diagnosed GBM are treated in the participating centers, of which about 280 (60%) would fulfill the inclusion/exclusion criteria of the trial. It is anticipated that about 260 of these patients would agree to participate and that it would be possible to recruit 210 patients in the 30-month recruitment period. Thus, recruitment of 136 patients seems feasible. The recruitment rate would be about one patient/center/month and centers would have to assess one to two/patients/month for eligibility.

Evaluation of results will be based on the Statistical Analysis Plan. Efficacy is measured by OS computed from the day of surgery until event or censored at last follow-up according to the Kaplan-Meier method with two-sided log-rank statistics for comparison. Primary efficacy analysis will be based on the intention-to-treat population; patients lost to follow-up are censored at the time of last contact. If required, a model-based Bayesian analysis for imputation of missing data will be used, and missing values imputed using the posterior predictive distribution of the model. In addition, a sensitivity analysis based on the per-protocol population will be performed.

All patients will be evaluated for safety; assessment of safety will be based on descriptive and explorative methods. For explorative analyses of secondary endpoints, classical statistical tests will be applied (e.g., log-rank test for survival data (PFS), chi-square/Fischer’s exact test for categorical data and *t* test/Mann-Whitney *U* test for continuous data). In addition, 95% confidence intervals will be calculated when applicable.

A Cox regression model will be used for explorative analysis of overall survival and progression-free survival with the covariates (1) treatment group, (2) recursive partitioning analysis classes I–IV as defined by Mirimanoff et al. [69] and de Vleeschouwer et al. [70], which already have been documented to influence outcome of standard as well as of vaccination therapy, the prognostic markers, (3) MGMT promotor methylation status, (4) extent of resection (complete vs. near-complete), (5) age, (6) center, (7) dexamethasone medication and (8) the therapeutic intervention in case of tumor progression. Subgroups of vaccinated patients will also be defined based on their immunological responsiveness as well as immunosuppressive scores (see below).

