## Methods

### Study design

This is a national, prospective, multicenter, open-label, randomized phase II study with two parallel groups, with the participating hospitals being located in the state of North Rhine-Westphalia in the proximity of Düsseldorf (a list of participating centers can be obtained from the sponsor or the registry). In the active recruitment period of 30 months, 136 patients with newly diagnosed, isocitrate dehydrogenase (IDH) wildtype, primary GBM [55] will be randomized at a 1:1 ratio after near-complete resection and successful production of tumor lysate. For a patient to be enrolled, all eligibility criteria (see below) must be met and free vaccine production capacity has to be available (enrollment may have to be paused). Enrollment of a patient is initiated by an investigator submitting by fax the Randomization Request Form to the Coordination Center for Clinical Trials, which will perform the randomization and inform the investigator of the outcome and allocation of the patient to the control or the vaccination arm of the study. The randomization list has been generated by the Coordination Center for Clinical Trials, using randomly selected block sizes of 4, 6, 8 and 12 patients. It will be centrally applied with concealment by the Coordination Center for Clinical Trials. The assignment to the two groups will be stratified according to O6-methylguanine-DNA-methyltransferase promotor methylation status, because it is an independent prognostic factor in TMZ chemotherapy [2, 56].

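### Allocation is stratified by MGMT status, but the interim and primary overall survival tests are named only as a log-rank test without strata; stratifying them would recover a little power at almost no cost

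*Protocol article*

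**What the plan says.** The Study design section of the protocol article states: "The assignment to the two groups will be stratified according to O6-methylguanine-DNA-methyltransferase promotor methylation status". The reason follows at once: "because it is an independent prognostic factor in TMZ chemotherapy".

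The overall survival (OS) test is then described in three places, none of which mentions strata:

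- **Interim rule (Study design).** At about half of the 87 expected events, efficacy is concluded if the two-sided log-rank p value is below 0.003.
- **Power statement (Sample size considerations and statistical analysis).** "a 0.050-level two-sided log-rank test for equality of survival curves will have 80% power", for medians of 14.6 and 26.6 months ("hazard ratio for death, 0.55").
- **Primary analysis (same section).** OS is analysed "according to the Kaplan-Meier method with two-sided log-rank statistics for comparison".

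The only analytic use given to MGMT status is as one of eight covariates in a Cox model labelled exploratory. The section also says: "Evaluation of results will be based on the Statistical Analysis Plan". That plan is not shown.

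**The concern.** Stratified allocation balances the arms on MGMT, so the difference between arms varies less from trial to trial than under simple randomisation. A plain log-rank test does not use this. Its variance still treats survival differences between methylated and unmethylated patients as random noise. Two consequences follow if MGMT is strongly prognostic: the true type I error falls below the nominal 5%, and power falls below what the same patients and deaths could give. The pooled hazard ratio also lies closer to 1 than the ratio within strata.

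What is at stake is efficiency and clarity, not false-positive risk. The trial is sized at 80% power for a large assumed effect, so it has little slack. It is also open-label with a formal efficacy interim, so the choice between a plain and a stratified test should be visible before deaths accumulate.

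**Working it through.** **1. The plan's own figures.** Inputs: two-sided alpha 0.05, power 80%, 1:1 allocation, medians 14.6 and 26.6 months.

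- Hazard ratio: 14.6/26.6 = 0.549.
- Events (Schoenfeld): 4(1.960 + 0.842)²/(ln HR)² gives 87.24 at 0.549 and 87.84 at 0.55.
- Power at 87 events: 79.9% at 0.549 and 79.6% at 0.55.
- Sample size: 2 × 61 = 122, and 122/0.90 = 135.6, rounded up to 136.

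So 87 events, 80% power and 136 patients all reproduce. The calculation is that of an ordinary log-rank test without strata.

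**2. Plain against stratified test.** From the article: 136 patients, 30 months' accrual (taken as uniform), MGMT-stratified blocks of 4, 6, 8 and 12, and analysis at 87 deaths. Assumed, because the article gives neither figure: 35% or 45% methylated, and a methylation hazard ratio from 1.0 to 0.4. Survival was exponential within strata, with an overall control median of 14.6 months and a treatment hazard ratio of 0.549 in each stratum, which keeps the overall vaccine-arm median at 26.6 months. Each cell has 10,000 trials, with both tests applied to the same trials. Where two values are given, they are for 35% / 45% methylated.

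| Methylation HR | Power, plain | Power, stratified | Two-sided type I error, plain | Type I error, stratified |
|---|---|---|---|---|
| 1.0 | 79.9% / 79.6% | 79.4% / 79.1% | 0.053 / 0.050 | 0.052 / 0.052 |
| 0.7 | 77.9% / 78.4% | 78.4% / 78.6% | 0.047 / 0.048 | 0.048 / 0.052 |
| 0.5 | 75.8% / 76.2% | 78.5% / 78.8% | 0.046 / 0.041 | 0.052 / 0.052 |
| 0.4 | 73.9% / 72.4% | 78.7% / 78.2% | 0.037 / 0.039 | 0.050 / 0.052 |

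Monte Carlo standard error is about 0.4 points for power and 0.2 points for type I error. The gaps in power are:

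- HR 0.7: 0.5 and 0.2 points.
- HR 0.5: 2.7 and 2.6 points.
- HR 0.4: 4.8 and 5.8 points.
- HR 1.0: the stratified test loses 0.5 points.

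Two separate simulations with 136 patients and 40% methylated agree to within a point or so. Plain against stratified power was 79% and 80% at HR 0.6 (one simulation). At HR 0.5 it was 77% and 79% in one and 75% and 79% in the other. At HR 0.4 it was 75% and 79%, then 75% and 80%.

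**3. If 0.55 is read as the overall hazard ratio.** With a within-stratum ratio of 0.549, the average overall ratio in these simulations was 0.560 at methylation HR 0.5 and 0.571–0.575 at 0.4. Stronger within-stratum effects were therefore also simulated. At methylation HR 0.4 with 35% methylated, overall ratios of 0.554 and 0.530 gave plain power of 77.9% and 84.1%, and stratified power of 82.3% and 87.9%. Interpolating to 0.549:

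- Plain: 77.9 + (0.005/0.024) × 6.2 = 79.2%.
- Stratified: 82.3 + (0.005/0.024) × 5.6 = 83.5%.

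On this reading the plain test delivers its stated power, and stratifying adds about 4 points.

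**The case against.** The strongest reply is that the article never calls the test unstratified. It is a condensed account that defers to an unseen analysis plan, and the strata of a log-rank test are a detail that an article may leave there. This stands: a reader might infer that the trial has ruled out stratification, and the document cannot show that. What remains is that the article names the test three times without strata and does give MGMT an analytic role, but only an exploratory one.

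A reader might also infer that the sample size or the 80% power is wrong. It is not. The design calculation and the named test agree, and the sample size never counted on a gain from stratification. Nor is the plain test invalid, since its type I error is at or below nominal apart from simulation noise.

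A third tempting reading is that the trial will report a biased hazard ratio. No unadjusted hazard ratio is planned. The only model described includes MGMT, and a pooled and a within-stratum ratio are different quantities rather than a wrong and a right one.

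Finally, the size of the gain rests on MGMT figures from outside the article, and it is negligible if the effect is modest. Stratifying also thins the data at the interim: of about 43 deaths, some 11–14 would fall in the methylated stratum at methylation ratios of 0.4–0.6. These limits are accepted. They reduce the point to a cheap improvement but do not remove it.

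**Conclusion.** The point holds as a matter of efficiency and clarity. If run as worded, the OS test ignores the one factor used to stratify allocation, a factor that the article itself calls prognostic. The test would remain valid but mildly conservative. With 35–45% methylated, the power forgone is about 0–1 points at a methylation hazard ratio of 0.6–0.7, about 2–3 at 0.5 (one smaller check gave 4) and about 4–6 at 0.4. Two-sided type I error is about 0.04 at ratios of 0.4–0.5.

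These sizes depend on an assumed methylated share and effect, exponential survival and a common treatment effect across strata. The article asserts that MGMT is prognostic but not how strongly, so the gain could lie anywhere in that range. The 87 events and 80% power stand for a plain log-rank test on the overall hazard ratio.

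**What to change.** In the interim paragraph of Study design, and in the primary analysis paragraph of Sample size considerations and statistical analysis, state that the interim and final OS tests are two-sided log-rank tests stratified by MGMT status as randomised. Add that the hazard ratio and its 95% confidence interval come from a Cox model stratified by MGMT, and that the unstratified log-rank test is a sensitivity analysis. If the analysis plan already says this, align the protocol wording with it.

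The cost is about a sentence in each section. No new data are needed: equivocal MGMT status is an exclusion criterion, so every eligible patient belongs to one of two strata. The event target can stay at 87. The statistical price is up to about half a power point if MGMT had no prognostic effect.

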### Eligibility criteria

All inclusion and exclusion criteria (Table 1) will be evaluated by the local investigators (neurosurgeons and/or neuro-oncologists) and in case of residual tumor volume after surgery and diagnosis/tumor cell content of tumor sample confirmed by central neuroradiologist and neuropathologist, respectively.

**Table 1 Tab1:** Inclusion and exclusion criteria

Key inclusion criteria	Key exclusion criteria
Newly diagnosed, monofocal GBM, isocitrate dehydrogenase wildtype (WHO grade IV; [57]) histologically confirmed by central neuropathologist	Medical history of severe acute or chronic disease with poor prognosis, autoimmune disorder, immunodeficiency, organ allograft or prior malignancy (≤ 3 years)
Near-complete resection (≤ 5 ml residual tumor volume) confirmed by central neuroradiologist on magnetic resonance imaging (MRI) scan within 72 h postoperative	Infection with human immunodeficiency virus, hepatitis B virus, hepatitis C virus or *Treponema pallidum* or other severe infection requiring hospitalization or i.v. antibiotics or anti-viral treatment (≤ 2 weeks)
Patients ≥ 18 years of age	Known allergy or intolerability to TMZ or any component of the capsules, dacarbazine, the contrast agent or the DC vaccine
Karnofsky performance status ≥ 70%	History of bleeding diathesis or coagulopathy
Sterile tumor sample of ≥ 150 mg with tumor cell frequency ≥ 60%, as determined by central neuropathologist, available for vaccine production	Preexisting myelosuppression
Successful production of sterile, avital tumor lysate	Previous radiotherapy to head and neck
Systemic corticosteroids tapered down to ≤ 2 mg of dexamethasone or equivalent per day within 7 days postoperative	Previous (≤ 6 weeks. or ≤ 5 half-lives) treatment with specific immunostimulatory agent
Adequate hepatic, renal, liver and bone marrow function and blood coagulation	Previous (≤ 4 weeks) treatment with live, attenuated vaccine
Use of highly effective contraception	Treatment of GBM in another clinical trial with therapeutic intervention or current use of any investigational agent
Signed informed consent	Known pregnancy or breast-feeding
	O6-methylguanine-DNA-methyltransferase promoter methylation status equivocal

Legend: *DC* dendritic cell, *GBM* glioblastoma multiforme, *i.v.* intravenous, *TMX* temozolomide, *WHO* World Health Organization

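### The primary survival comparison leaves out age and extent of resection, both known before randomisation: a modest, avoidable loss of efficiency, not an error

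*Protocol article*

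**What the plan says.** All references are to the protocol article.

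- *Sample size considerations and statistical analysis* sets the primary overall survival (OS) analysis in the intention-to-treat population "according to the Kaplan-Meier method with two-sided log-rank statistics for comparison". No covariate or stratum is named for it.
- The same section sizes the trial on that test: "a 0.050-level two-sided log-rank test for equality of survival curves will have 80% power", for "a median OS in the control group of 14.6 months vs. 26.6 months in the test group", with 87 deaths.
- Covariates appear only in a separate model: "A Cox regression model will be used for explorative analysis of overall survival and progression-free survival with the covariates". The list includes "extent of resection (complete vs. near-complete), (5) age" directly after MGMT status, under the label of prognostic markers. It also contains centre, dexamethasone with no time point, and the therapy chosen at progression.
- *Eligibility criteria* (Table 1) makes near-complete resection an entry condition, with at most 5 ml "residual tumor volume) confirmed by central neuroradiologist on magnetic resonance imaging" within 72 hours of surgery. Age is also an entry item.
- *Study design* places randomisation after resection and stratifies it by MGMT status only. The interim efficacy boundary there is a log-rank p value below 0.003.

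**The concern.** In a proportional hazards setting, leaving out baseline factors that predict death pulls the treatment hazard ratio towards 1 and lowers power, even when the arms are perfectly balanced. Age and extent of resection are not balanced by design. Their effect therefore stays in the primary comparison as unexplained variation, whether or not that test is stratified by MGMT.

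The trial has one confirmatory comparison with a fixed 87 deaths and about 80% power, so there is little margin. The information needed to recover some power is known before allocation. The article assigns the log-rank test to the primary analysis and the Cox model to exploration, so this is a stated choice and not a detail left to the statistical analysis plan.

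**Working it through.** **1. The plan's own figure.** Inputs are two-sided alpha 0.05, power 80%, 1:1 allocation and "hazard ratio for death, 0.55" (14.6/26.6 = 0.549). Schoenfeld's formula is D = 4(z₀.₉₇₅ + z₀.₈₀)² / (ln HR)².

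- HR 0.55: 4(1.960 + 0.842)² / (0.598)² = 87.8 deaths.
- HR 14.6/26.6: 87.2 deaths.
- Power at 87 deaths and HR 0.55: Φ(0.598 × √87 / 2 − 1.960) = Φ(0.83) = 79.6%.

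The stated 87 reproduces.

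**2. Assumptions for the gain.** The documents give no prognostic hazard ratio for age or resection, so strength is assumed. It is expressed as the standard deviation (SD) of the two factors' combined log-hazard. Three simulations were run, each with 61 patients per arm and analysis at 87 deaths.

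- **A:** 30-month uniform accrual, two normally distributed covariates, MGMT prevalence 45% with log HR −0.6. Both analyses are stratified by MGMT. 4,000 to 6,000 runs.
- **B:** 30-month uniform accrual, age hazard ratio per SD of 1.2, 1.35 or 1.5, and near-complete versus complete resection hazard ratio of 1.3, 1.5 or 1.8 with 35% near-complete. The combined SD is √[(ln HR_age)² + 0.35 × 0.65 × (ln HR_res)²]. For the weak case this is √(0.0332 + 0.0157) = 0.22; the other two give 0.36 and 0.49. MGMT has either no effect or a hazard ratio of 0.5 with 40% methylated. 2,000 runs (4,000 in step 4).
- **C:** medians 14.6 and 26.6 months, no MGMT effect, 2,500 runs.

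**3. Power at a conditional hazard ratio of 0.55.**

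| Simulation | SD | Log-rank | Adjusted Cox | Gain (points) |
|---|---|---|---|---|
| A | 0.30 | 75.2% | 77.8% | 2.6 |
| A | 0.40 | 72.7% | 78.1% | 5.4 |
| A | 0.50 | 69.6% | 77.7% | 8.1 |
| B, no MGMT effect | 0 | 78.7% | 77.6% | −1.1 |
| B, no MGMT effect | 0.22 | 77.2% | 78.8% | 1.6 |
| B, no MGMT effect | 0.36 | 72.8% | 76.9% | 4.1 |
| B, no MGMT effect | 0.49 | 68.8% | 77.0% | 8.2 |
| B, MGMT HR 0.5* | 0.22 | 75.6% | 78.6% | 3.0 |
| B, MGMT HR 0.5* | 0.36 | 74.0% | 78.1% | 4.1 |
| B, MGMT HR 0.5* | 0.49 | 69.0% | 78.2% | 9.2 |
| C | 0 | 78% | 78% | 0 |
| C | 0.2 | 77% | 79% | 2 |
| C | 0.3 | 76% | 79% | 3 |
| C | 0.5 | 69% | 78% | 9 |

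*MGMT-stratified log-rank against Cox with age, resection and MGMT as a covariate. At 2,000 runs each power figure has a standard error of about √(0.77 × 0.23 / 2000) = 0.9 points.

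**4. Effect strengthened so that the log-rank test has roughly 80% power.** The planned 0.55 comes from two group medians, so it is a marginal figure. This makes step 4 the fairer comparison.

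| Simulation | Weak | Moderate | Strong |
|---|---|---|---|
| A | 80.1 → 82.8% (2.7) | 81.5 → 85.9% (4.4) | 80.1 → 87.2% (7.1) |
| B, no MGMT effect | 79.6 → 80.8% (1.2) | 79.2 → 83.0% (3.8) | 83.1 → 89.3% (6.2) |
| B, MGMT HR 0.5* | 82.2 → 83.7% (1.5) | 83.7 → 87.5% (3.8) | 86.2 → 92.5% (6.3) |

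**5. Type I error.** In A, one-sided rejection under the null was 2.5% to 2.9%. In B, two-sided rejection was 4.0% to 5.8% for the plain log-rank test and for Cox with age and resection (standard error about 0.5 points). With MGMT also in the Cox model it was 4.8% to 6.5%, averaging 39.1/7 = 5.6% over seven settings. The MGMT-stratified log-rank test averaged 37.9/7 = 5.4% on the same data sets.

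**The case against.** The strongest reply is that nothing here is wrong. The log-rank test is valid and is used consistently for sample size, interim boundary and final analysis. Chance imbalance in a randomised comparison does not inflate type I error, because the null distribution already allows for it. An adjusted hazard ratio will be reported anyway. All of that stands, and it is why the point concerns efficiency only.

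Four further points also stand.

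- **The size is assumed.** Eligibility narrows the prognostic range (monofocal tumour, residual at most 5 ml, Karnofsky at least 70%), so the weak end is plausible.
- **Residual volume in ml may not be available.** The article shows a centrally confirmed threshold, not a recorded volume, and its own model codes resection as two categories. A linear ml term was not simulated.
- **Changing the primary test reaches further than one sentence.** The interim boundary and the power statement are both tied to the log-rank test.
- **Explicit support is uneven.** The article says outright that recursive partitioning class and MGMT status affect outcome. Age and resection are supported only by their place in a list that runs on to other items.

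What does not stand is that the explorative model already covers the need. It includes therapy at progression, which arises after randomisation, and dexamethasone with no time point. Its treatment estimate is therefore not a clean baseline-adjusted effect.

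**Conclusion.** The point holds as a worthwhile but optional improvement. At 87 deaths and a conditional hazard ratio of 0.55, adjustment adds about 0 to 3 power points if the two factors are weak and about 8 to 9 if they are strong. Calibrated to about 80% log-rank power, the gain is about 1 to 7 points. If the factors carry no prognostic information, the loss is at most about one point, which is close to simulation error. The direction agrees across all three simulations. The size rests wholly on assumed prognostic strength.

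Three stronger readings are tempting and unsupported.

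- A reader might infer that the trial is underpowered, from the log-rank figures of 69% to 77%. Those treat 0.55 as a conditional hazard ratio, whereas the plan derives it from group medians, and on its own terms the plan's calculation reproduces.
- A reader might infer that the primary test is biased or invalid. It is neither.
- A reader might infer that adjustment is free. It needs no extra patients, but it changes what the hazard ratio means and may require matching edits elsewhere.

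**What to change.** Before outcome data are seen, prespecify in *Sample size considerations and statistical analysis* a Cox model for OS with treatment, age as a continuous covariate and extent of resection as the plan already codes it (complete versus near-complete), stratified by MGMT. Use residual volume in ml only if it is recorded centrally. Allow only values fixed before randomisation, so leave out therapy at progression. The model can be used in either of two ways.

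1. **As the primary effect estimate, reported beside the log-rank p value.** The interim rule and power statement stay as they are. This is the lighter change.
2. **As the primary test.** The interim test in *Study design* and the power statement must then be aligned with it, and the log-rank result kept as a sensitivity analysis. The type I error of the exact model should be confirmed by simulation first, given the 4.8% to 6.5% seen with MGMT included.

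The cost is wording in the analysis plan, with the matching edits under the second option. No new patients are needed, and no new data if resection keeps its two categories. The one small downside is that the adjusted hazard ratio is conditional on the covariates and must be labelled so.
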